## 4.2 Eligibility Criteria

**Inclusion Criteria**

Subjects eligible for this clinical study must fulfill all of the following:

1. Age above 21 (men and woman);
2. Patient is admitted to ICU and expected to receive mechanical ventilation for more than 12 hours;
3. Absence of clear signs of pneumonia and lung contusion on chest X ray;
4. Connection of the ETT to the AnapnoGuard system less than 6 hours from intubation initiation;
5. No fever or fever from known from other non chest/lung origin;
6. ~~Signed informed consent by subject’s legally acceptable representative~~.

**Exclusion Criteria:**

Subjects not eligible for this research study include those that have any of the following:

1. Patients who have been treated with mechanical ventilation during the last 3 months;

2. Patients with facial, oropharyngeal or neck trauma

3. BMI>40

~~4. Any chest X-ray pathology during the first 24 hours post Intubation~~

4. Pregnant women

## 5. Patient ventilated in prone position

## 6. Difficult intubation (defined as more than 3 intubation attempts)

**Subject Withdrawal Criteria**

Subjects may be withdrawn from the study if any one or more of the following events occur:

1. Subject’s legally acceptable representative has the right to decide regarding subject withdrawing from the study at any time without providing any explanation.
2. Refusal of the subject’s nearest relative to continue follow-up observations.
3. Any significant adverse event that upon the investigator opinion may be related to the AnapnoGuard system.
4. Significant protocol deviation.
5. Less than 12 hours connection to the AnapnoGuard 100 system.
6. Any chest x-ray pathology during the first 12 hours post intubation.
7. Patients who underwent re-intubation

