**Time Table**

|  | **Screening** | **Connection to AnapnoGuard System** | **Mechanically Ventilation**  **Period** | **After AnapnoGuard Disconnection** | **Post Clearance Follow-up Phone Information** |
| --- | --- | --- | --- | --- | --- |
| **Time line** | **During hospitalization in ICU** | **Up to 6 h from intubation initiation** | **Daily evaluation** | **48h post extubation** | **1 month following extubation** |
| **Informed consent** | x |  |  |  |  |
| **Inclusion criteria** | x |  |  |  |  |
| **Medical history** | x |  |  |  |  |
| **Chest x-ray** | x | X | x* | x |  |
| **Blood tests** | x | X | x | x |  |
| **Vital signs** | x | X | x | x |  |
| **Trap bottle secretions***** |  |  | x |  |  |
| **Oxygen saturation** | x | x | x | x |  |
| **Mechanical complication assessment**** |  |  |  | x |  |
| **Subject’s general condition** |  |  | x | x | x |
| **AE and SAE** |  | x | x | x |  |
| **Study deviation** |  | x | x | x |  |
| **Final statistical analysis** |  |  |  | x |  |
| **Study exit** |  |  |  | x |  |

* Chest X-ray will be done at baseline, 48 hours after intubation and whenever there is clinical suspicion for VAP

** Mechanical complications assessment will include: spirometry, fiber optic in selected ICUs and questionnaire regarding throat pain and hoarseness.

***Recording level of trap bottle secretions 3 times a day (per shift). Records – Images and or electronic record

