## Primary Objective

The primary objective of this study is to evaluate the safety of using the AnapnoGuard 100 system during the course of mechanical ventilation and intubation in Intensive Care Unit (ICU).

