# 4. Selection and Withdrawal of Subjects

## 4.1Source of Subjects and Enrollment

Male/female subjects admitted to ICU and expected to be mechanically ventilated for at least 12 hours. A minimum of 12 hours of intubation is required due to the fact that the AnapnoGuard 100 system’s intended use is for patients with prolonged ventilation with endotracheal tubes. In order to evaluate the safety of the device, the subject should be intubated for at least 12 hours.

~~Only subjects that their legally acceptable representative have signed an Informed Consent Form and meet all of the eligibility criteria listed below will be qualified for enrollment. Upon recruitment, subjects will be randomized, using the sequentially numbered opaque sealed envelopes (SNOSE) randomization method, to be treated with AnapnoGuard system (Study Group) or to be treated according to the standard ICU procedure (Control Group).~~

Male/female subjects admitted to ICU and expected to be mechanically ventilated for at least 12 hours. Subjects will be randomized to study/control group prior to enrollment in blocks of ten (the first 10 subjects (1-10) will be selected for study group; the second 10 subjects (11-20) will be selected for the control group, and so on). Subjects will be intubated with either Hospitech’s ETT or Covidien’s ETT (10-10) and only after intubation they will be screened. Only subjects that meet all of the eligibility criteria listed below and their legally acceptable representative has signed an Informed Consent Form will be qualified for enrollment.

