# 8. Statistical Consideration

## 8.1 Safety Analysis Set

The safety analysis set will consist of all subjects for whom the study treatment was initiated. AE's will be tabulated by treatment arm, severity and relation to treatment.

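### Exclusion 6 (more than 3 intubation attempts) is applied after intubation with the assigned tube, so eligibility depends on an event the device may cause, and such patients can drop out of the primary safety proportion

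*Protocol*

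**What the plan says.** Section 4.2, Exclusion Criteria, item 6 (repeated in the Synopsis) excludes "Difficult intubation (defined as more than 3 intubation attempts". The order of events is set in section 4.1, in the text that replaces a struck-through paragraph: "Subjects will be randomized to study/control group prior to enrollment in blocks of ten". The patient is then intubated with the Hospitech or the Covidien tube, and "only after intubation they will be screened". Enrollment follows for "Only subjects that meet all of the eligibility criteria listed below" and whose representative has consented.

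Sections 6.3 and 6.4 describe another order. Screening comes before any study-specific procedure, and randomization comes after enrollment.

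Section 5.1.1 names the AnapnoGuard tube as one of three main components of the system, whose intended use is airway management by intubation. The Primary Objective is the "safety of using the AnapnoGuard 100 system during the course of mechanical ventilation and intubation in Intensive Care Unit". Section 3.1 scores a subject as a success if no device-related AE or SAE occurs during intubation. Section 8.1 defines the safety set as "all subjects for whom the study treatment was initiated". In the Time Table, the AE and SAE row is empty at Screening and is first marked in the column for connection to the system, timed "Up to 6 h from intubation initiation".

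**The concern.** The number of intubation attempts cannot be known until intubation has been tried. In the section 4.1 sequence those attempts are made with the assigned tube. A patient in whom the AnapnoGuard tube proves hard to place, and who may be hurt in the process, then becomes ineligible rather than a failure on the safety endpoint. Membership of the analysed cohort depends on something the device may have caused.

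Two consequences follow. The primary test in section 8.3 uses the AnapnoGuard arm alone, so removing failures raises the success proportion directly, and the control arm offers no correction. Section 3.1 also compares SAE incidence between arms. The two tubes differ, so the exclusion can remove different patients from each arm and disturb that comparison too. If events in excluded patients are not collected, no later analysis can restore them.

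**Working it through.** **Order of events.** The protocol contains two sequences.

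| | Section 4.1 | Sections 6.3 and 6.4 |
|---|---|---|
| 1 | Arm set | Screening and consent |
| 2 | Intubation with the arm's tube | Enrollment |
| 3 | Screening, including exclusion 6 | Randomization |
| 4 | Enrollment if eligible | Intubation with the arm's tube |

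Inclusion criterion 4 (connection less than 6 hours from intubation initiation) and section 6.1 (consent sought before connection, or as soon as possible after intubation for controls) fit the first column. In both columns the attempt count becomes known only after allocation and use of the assigned tube. They differ in the patient's status at that moment: not yet enrolled under section 4.1, already enrolled under section 6.4.

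**Whether the safety set catches these patients.** Section 8.1 would include them only if attempted insertion counts as initiating treatment and a patient excluded after intubation still counts as a subject. The protocol states neither. The Time Table does not settle when AE recording begins. The column can mean the whole window from intubation to 6 hours, or the moment of connection within it.

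**Illustration of the effect.** The protocol gives no figure to reproduce on this point and no rate of difficult intubation, so the counts below are assumptions.

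- From the documents: 60 patients in total, hence 60/2 = 30 per arm if split equally; success requires a one-sided lower 95% limit at or above 0.80 (section 8.3).
- Assumed: 30 patients intubated with the AnapnoGuard tube; k of them need more than 3 attempts, each with a device-related event; m other failures.
- All counted: x = 30 − k − m successes out of 30. After exclusion 6: the same x out of 30 − k.
- Exact (Clopper-Pearson) limit L: the value at which P(X ≥ x | n, L) = 0.05. When x = n this is 0.05^(1/n); for 27/27, 0.05^(1/27) = 0.895.
- Wald limit: p − 1.645·√(p(1−p)/n). For 27/30: 0.90 − 1.645·√(0.90·0.10/30) = 0.90 − 0.090 = 0.810.

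| k | m | Counted | Exact | Wald | Excluded | Exact | Wald |
|---|---|---|---|---|---|---|---|
| 2 | 0 | 28/30 | 0.805 | 0.858 | 28/28 | 0.899 | 1.000 |
| 3 | 0 | 27/30 | 0.761 | 0.810 | 27/27 | 0.895 | 1.000 |
| 2 | 1 | 27/30 | 0.761 | 0.810 | 27/28 | 0.841 | 0.907 |
| 3 | 1 | 26/30 | 0.720 | 0.765 | 26/27 | 0.836 | 0.903 |

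With the exact limit, the conclusion reverses at k = 3 with no other failure, or at k = 2 with one other failure. With the Wald limit it does not reverse in either case, and among these rows it reverses only at k = 3 with one other failure. The protocol names no interval method for the test; it mentions the normal approximation only for the power calculation.

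**The case against.** The best counter-argument is about scope. The protocol often uses intubation for the state of being intubated. Section 1 says the complications of interest relate to cuff pressure during prolonged ventilation, and the table of potential adverse events in section 9.3 lists cuff and suction problems but no heading for insertion injury. On that view exclusion 6 simply defines the population. This shows where the emphasis lies, but it does not remove the problem. The endpoint in section 3.1 is any device-related AE or SAE, and the tube is part of a device intended for intubation.

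Three stronger readings are tempting, and the documents do not support them.

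- *Insertion injuries in excluded patients are never recorded.* This is not established. The Time Table column can be read as starting at intubation, section 9.4 requires any study event judged an AE to be recorded, and section 8.1 could be read to cover attempted insertion. The text is ambiguous.
- *All insertion problems are screened out.* Injuries within 3 attempts are kept. A difficult intubation may also be due to the patient's anatomy; the criterion does not separate the two causes.
- *The trial would pass when it should fail.* That rests on assumed counts, on every such patient having a related injury, and on the exact limit. It also treats excluded patients as using up the 30 places. If they were replaced, the comparison for k = 3 would be 30/30 against 30/33 (exact limits 0.905 and 0.782).

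It is also fair to say that under section 6.4 the patient is already enrolled and randomized, so the screen-failure route depends on section 4.1. That conflict has to be resolved either way.

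**Conclusion.** The concern holds in a limited form. Followed as written, section 4.1 makes eligibility depend on an event that occurs after exposure to a component of the investigational device. Exclusion 6 can then remove device-related insertion failures of more than 3 attempts from the primary safety proportion, possibly differently by arm. Sections 6.3, 6.4 and 8.1 and the Time Table neither confirm nor prevent this.

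The size cannot be stated, because the protocol gives no rate of difficult intubation or of injury from it. The illustration shows only that, with about 30 patients in the tested arm, two or three such patients can be enough to change the conclusion, depending on the interval method and the number of other failures. Whether difficult intubation should be a clinical exclusion is a matter for the sponsor and is not judged here.

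**What to change.** 1. Reconcile section 4.1 and exclusion 6 with sections 6.3 and 6.4, so that the protocol gives one order of allocation, intubation, screening, consent and enrollment.
2. In section 8.1, define treatment initiation as the first attempted insertion of the assigned tube. All such patients, subject to consent, then belong to the safety set and the success denominator, including those later found to meet exclusion 6.
3. In both arms, record the number of attempts, and record adverse events from the first attempt. Align the AE and SAE row of the Time Table with this.
4. Report the number of patients excluded under criterion 6 by arm.

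The cost is amendment wording and one added CRF field. The success rate may look slightly less favourable, because some patients with difficult insertions will now be counted.

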## Handling of Withdrawals

In accordance with the current revision of the Declaration of Helsinki, a subject’s legally acceptable representative has the right to decide regarding subject withdrawing from the study, at any time, for any reason, without prejudice to the subject’s future medical care by the physician or the institution. The investigator and the sponsor also have the right to withdraw subjects from the study in the event of serious adverse events, protocol departure, or other reasons. Should a subject’s legally acceptable representative decide to withdraw, all efforts will be made to collect and report the final visit observations, and the reasons for withdrawal, as thoroughly and timely as possible.

Withdrawals will be recorded, analyzed and reported to local IRB or ethical committees.

# 5. MATERIALS

## 5.1 Study Group: AnapnoGuard 100 system

## 5.1.1 Intended use

***AnapnoGuard™ 100 Respiratory Guard*** Systemis intended for airway management by oral/nasal intubation while providing continuous endotracheal cuff pressure control using non-invasive measurement and monitoring of carbon dioxide concentration in the subglottic space and evacuation of secretions from above the endotracheal tube’s cuff.

The system comprises of the following main three components:

- AnapnoGuard 100 control unit
- Single use AnapnoGuard endotracheal tube with two suction lumens and a vent lumen
- Single use AnapnoGuard interface harness and filters kit

##

## 5.1.2 Identification of the Investigational Medical Devices

The investigational AnapnoGuard 100 system will be labeled for use in clinical trials only. The label includes trade name and address of the manufacturer, Serial Number and all other required information.

## 5.2 Control Group:

# The Control group will be intubated with the TaperGuard EVAC endotracheal tubes ID 8mm by Covidien. After the intubation, patients in the control group will be connected to the Boehringer CASS regulator (Continuous Aspiration of Subglottic Secretion) until extubation.

# 6. STUDY PROCEDURES - METHODS

## 6.1 Informed Consent Procedure

- - In obtaining and documenting informed consent, the investigator should comply with the applicable regulatory requirements, and should adhere to GCP, HIPAA and to the ethical principles that have their origin in the Declaration of Helsinki.
  - Prior to the beginning of the trial, the investigator should have the Ethics Committee written approval/favorable opinion of the written informed consent form and any other written information to be provided to subject’s legally acceptable representative.
  - The written Informed Consent Form (ICF) and any other written information to be provided to subjects legally acceptable representative should be revised whenever important new information becomes available that may be relevant to the subject’s consent. Any revised written ICF and written information should receive the Ethics Committee’s approval/favorable opinion in advance of use. The subject or the subject’s legally acceptable representative should be informed in a timely manner if new information becomes available that may be relevant to the subject’s willingness to continue participation in the trial. The communication of this information should be documented.
  - Neither the investigator, nor the trial staff, should coerce or unduly influence a subject’s legally acceptable representative to participate or to continue to participate in a trial.
  - The investigator, or a person designated by the investigator, should fully inform the subject’s legally acceptable representative, of all pertinent aspects of the trial including the written information given approval/favorable opinion by the Ethic Committee.
  - Before informed consent may be obtained, the investigator, or a person designated by the investigator, should provide the subject’s legally acceptable representative ample time and opportunity to inquire about details of the trial and to decide whether or not to participate in the trial. All questions about the trial should be answered to the satisfaction of the subject's legally acceptable representative.
  - ~~Prior to a subject’s participation in the trial,~~ the written ICF should be signed and personally dated by the subject's legally acceptable representative, and by the person who is authorized to conducted the informed consent discussion.
  - ~~Prior to participation in the trial,~~ the subject's legally acceptable representative should receive a copy of the signed and dated written ICF and any other written information provided to the subjects. During a subject’s participation in the trial, the subject’s legally acceptable representative should receive a copy of the signed and dated consent form updates and a copy of any amendments to the written information provided to subjects.
  - Subject's legally acceptable representative must provide informed consent and sign and date with his hand writing an ICF prior to any study related procedures being performed. The person reviewing the ICF with the subject must also sign and date the ICF. Each of the signers must sign and date in the presence of the other signer.
  - Allocated informed consent study staff will make efforts to obtain written informed consent prior to enrollment (for study patients – Before connection to the AnapnoGuard 100 system and for control patients - as soon as possible following intubation). Nevertheless, for specific cases (e.g. patients arriving at the ICU without an accompanying legal representative, there will be a 24 hour window to achieve written informed consent. The reason for enabling a 24 hour window for written ICF in the control group has to do with the fact that these patients will be treated with conventional standard of care. A 24 hour written ICF is allowed for the study group as well as for the control group since the investigational device, the AnapnoGuard 100 respiratory system, is a commercially (CE Mark) available device that is intended for non-life supporting functions and performs the following two basic operations; cuff pressure control and suctioning above the cuff.

## 6.2 Study Time Line

Study procedure will take place in the Intensive Care Unit, and will continue at least 48 hours following disconnecting from the AnapnoGuard system. Study duration for each subject depends upon mechanical ventilation duration, which will be defined by subject’s general condition (not depended upon study procedure). Altogether, study duration will be approximately 12 months, depending on subject recruitment rate.

### 6.3 Screening procedure

The following will be collected or performed before any study-specific procedures are performed:

- Ensure that all inclusion criteria are met.
- Obtain Informed Consent Form (the individual conducting the informed consent process must also sign the consent form and document it in the subject’s source record).
- Obtain blood count lab tests.
- Obtain chest X-ray.
- Obtain demographics (age, family history, and gender),
- Complete physical examination, current medications that subject is using, and medical and surgical history (anamnesis).
- Assign a sequentially ordered subject number per each site (which will specify the site and subject number). If a subject withdraws or is withdrawn from the Study or fails to undergo procedure, the subject number cannot be reassigned.
- Inform the study monitor about the subject’s recruitment and the planned date of treatment.

### 6.4 Connection to ETT, Operation and Monitoring Procedure

Following enrollment, subjects will be randomized to a study group or control group using the block randomization method. Treatment will be as follows:

- The study group patients will be treated with the AnapnoGuard 100 system and will be intubated with the AnapnoGuard's ETTs.

## The control group patients will be intubated with the TaperGuard EVAC endotracheal tubes by Covidien.

6.5 Treatment of study Group

Patients assigned to the study group, will be connected to the AnapnoGuard 100 system. The AnapnoGuard tubes (AnapnoGuard endotracheal tubes, Hospitech Respiration LTD, Petach-Tikva, Israel) will be used for intubation (ETT). Once connected to the AnapnoGuard 100 system, optimal cuff pressure will be set automatically according to CO2 level measured by the AnapnoGuard system in the subglottic space between the ETT cuff and the vocal cords. In addition, the AnapnoGuard system will perform programmed, Intermittent Aspiration of Subglottic Secretions below the vocal cords using the two suction lumens of the ETT. Optimal cuff pressure determination will be performed every 20 minutes (default) or according to the AnapnoGuard 100 algorithm. Cuff pressure and any change in cuff pressure will be automatically recorded by the AnapnoGuard 100 data logger system.

6.6 Treatment of control group

Cuff pressure will be set by manometer according to the physician judgment. Cuff pressure will be measured and set at least once daily. In case of using suction ET tubes, suction will be performed manually or by the use of the Boehringer 3720 CASS regulator, according to the manufacture instructions.

**6.7 Data collection**

The following parameters will be recorded with respect to the optimal cuff pressure:

- Patient position
- Ventilator parameters will be recorded (the setting will be done according to the physician clinical judgment):
- Assist vs. Control ventilation
- Pressure vs. Volume controlled ventilation
- Peak inspiratory pressure
- Peak end expiratory pressure (PEEP)
- Respiratory rate
- Vital signs will be recorded every 4 hours (blood pressure and temperature);
- Chest x-ray will be obtained on a daily basis;
- Blood test for white blood cell count and differential;
- Medication; special emphasis on antibiotic use.
- Daily recording of the amount of secretions in the AnapnoGuard trap bottle.
- Oxygen saturation;
- Oxygen concentration;
- Any interventional procedure performed by the medical staff;
- Any disconnection from the AnapnoGuard system;
- Study deviations will be documented if applicable;
- Adverse events will be managed and documented.

